### Study Procedures

After screening, eligible participants will be enrolled and they will complete baseline assessments. Thereafter, participants will be randomly assigned to either an EA experimental group or a sham control group. EA or sham treatments will be given twice weekly for 8 weeks—a total of 16 sessions. Participants in both groups will receive routine chemotherapy provided by their oncologists, which will include the use of cytotoxic drugs. Participants will be assessed at the following timepoints (see Figure 2): baseline (T0), midpoint of main treatment (T1-T3) once every 2 weeks, and end of the 8-week main treatment (T4). Assessments include MoCA [24] + Functional Assessment of Cancer Therapy-Cognitive function (FACT-Cog) [25] for cognitive performance, FACT/Functional Assessment of Chronic Illness Therapy-Fatigue (FACIT-Fatigue) [26] for fatigue, European Organization for Research and Treatment of Cancer QoL Questionnaire-Core 30 (EORTC QLQ-C30) [27] for QoL, and Functional Assessment of Anorexia-Cachexia Therapy (FAACT)/FACT-Biologic Response Modifier (FACT-BRM) [28] for chemotherapy-related side effects. Assessments will be done prior to any procedures in that visit, including disease assessment and physician consultation.

### Randomization and Allocation Concealment

Older patients with tumors will be screened for eligibility, and enrollment and baseline assessments should be completed thereafter. A random code of simple, complete, and nonsequential numbers could be produced in advance from a computer-generated block randomization with random block sizes. Participants will be randomly assigned to experimental or control groups in a 1:1 ratio. Random information will be sealed in sequentially numbered opaque envelopes.

### Blinding

Only the acupuncturist can open the envelope after the participant’s completion of baseline assessments. Participants and all other researchers will be blinded to group assignments. Participants are informed that they have a similar chance of allocation to any group and will be blinded to group assignments. A clinical assessor will be arranged to conduct assessments on a day different from the day of acupuncture treatment to avoid cross communications among the assessors, acupuncturists, and participants. An eye mask will be used to avoid communications among participants during EA treatment.

### Interventions

Potentially eligible patients will be recruited through clinical oncologists’ referral from local hospitals and advertisements. Research staff are notified once a participant completes the baseline assessment. The interventions of the experimental and control groups will be performed in the Department of Medical Oncology, Nanjing First Hospital, Nanjing Medical University, Nanjing, Jiangsu, China. Registered Chinese medicine acupuncturists at the Division of Chinese Medicine will be recruited who will be responsible for delivering treatment according to STRICTA (Standards for Reporting Interventions in Clinical Trials of Acupuncture) [29].

### Acupuncture Group

Participants in the experimental group will receive EA treatment. Acupuncture intervention will be conducted for 2 sessions per week over 8 consecutive weeks. Assessments will be conducted at baseline and once biweekly thereafter. For the experimental group, acupuncture points are mainly on the head, limbs, and abdomen, with a total of 6 pairs of electrically charged needles on the head, while for the control group, acupuncture points are mainly on the head and limbs, with only a pair of electrically charged needles on the head. The acupuncture points are as follows: Baihui point, left Shencong point, right Shencong point, bilateral Shuaigu point, bilateral Touwei point, bilateral Toulin point, bilateral Taiyang point, Yintang point, Zhongwan point, Qihai point, bilateral Waiguan point, bilateral Shenmen point, bilateral Hegu point, bilateral Zusanli point, bilateral Fenglong point and bilateral Sanyinjiao point. A total of 6 pairs of electrodes from the electric stimulator (CMNS6-3; 2-5 Hz, continuous wave) will be connected to the end of the needles. The 6 fixed points are Baihui and Yintang, left Shencong and left Toulin, right Shencong and right Toulin, left Shuaigu and right Shuaigu point, left Touwei and right Touwei points, and left Taiyang and right Taiyang (see Figure 3).

**Figure 3 figure3:**
[figure not shown]
Acupoints for electroacupuncture stimulation.

Disposable acupuncture needles (0.30 mm in diameter and 25-40 mm in length) will be inserted at a depth of 10-30 mm perpendicularly or obliquely into the acupoints. Manual manipulation will be performed for all acupoints to evoke needling sensation. Electrical stimulation will be additionally delivered on the 6 pairs of the frontal acupoints. The output peak current and voltage of the machine would be 6 V and 48 mA, respectively, with constant waves at frequencies of 2 Hz and phase duration of 100 µs for 30 minutes. Electrical stimulation will last for 30 minutes. The needles on body acupoints will also be retained for 30 minutes. Upon needle withdrawal, the points will be compressed with iodine volts swabs to prevent bleeding [30].

### Control Group

The control treatment procedure is the same as that in the experimental group, except that only a pair of electric needles will be selected for the electrical stimulation on the head. After completing the 8-week acupuncture intervention, patients in the control group will be administered follow-up EA acupuncture free of charge. The same 16 sessions or a total of no more than 8 weeks of acupuncture will be performed as compensation.

### Assessments

In this study, therapeutic efficiency will be assessed in terms of the following aspects: cognitive performance, fatigue, QoL, and chemotherapy-induced side effects. The primary outcome of this study is to verify whether EA is therapeutically useful for preventing chemobrain and alleviating the related symptoms and the safety of intervention. Cognitive performance will be assessed using MoCA + FACT-Cog. The secondary outcomes are as follows: QoL will be measured using EORTC QLQ-C30, fatigue will be assessed using the FACIT-Fatigue scale, and the manifestation of chemotherapy-induced side effects will be assessed using the Chemotherapy Symptom Rating Scale FAACT + FACT-BRM. All assessment scales will be evaluated by previously trained researchers at the following timepoints (see Figure 2): baseline (T0), midpoint of main treatment (T1-T3) once every 2 weeks, and end of the 8-week main treatment (T4) (a total of 5 timepoints). We will also keep a record of all the shedding cases. This study is a multidisciplinary clinical trial (across oncology and Chinese medicine disciplines) on the role of Chinese acupuncture as therapy for chemotherapy-induced cognitive impairment in older patients with cancer. If successful, findings from this study might have beneﬁts in reducing chemotherapy-induced working memory impairment. Data from this study may be used to support an implementation and dissemination trial of Chinese EA in real-world behavioral health and social service settings.

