**Results:**

Eligible participants will be randomized to the control group or the experimental group in 1:1 ratio. The primary outcome of this intervention will be the scores of the Montreal Cognitive Assessment. The secondary outcomes, that is, attentional function and working memory will be determined by the Digit Span Test scores. The quality of life of the patients and multiple functional assessments will also be evaluated. These outcomes will be measured at 2, 4, 6, and 8 weeks after the randomization.

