Emerging chemotherapy-induced cognitive impairments in older patients with cancer are likely to widen without proper early intervention tactics. In this protocol, we propose a 2-arm, prospective, randomized, assessor-blinded trial to examine the efficacy and safety of EA for chemobrain among older patients with cancer who are on or about to receive chemotherapy. The aim of this study directly contributes to the existing knowledge in this area, thereby establishing a basis for further research. Changes in the scores on MoCA [17] and the incidence of adverse events serve as the primary outcome. Scores on the Digit Span Test will be the secondary outcome for attentional function and working memory [18]. The QoL and multiple functional assessments will also be evaluated [19]. Outcomes include the MoCA, Digit Span Test, QoL, and multiple functional assessments at 2, 4, 6, and 8 weeks after randomization. Data from this efficacy trial will determine whether Chinese EA successfully improves the symptoms of chemobrain and whether these improvements could markedly reduce the various side effects caused by cytotoxic chemotherapy drugs. If successful, findings from this study might have beneﬁts in reducing chemotherapy-induced working memory impairment. Data from this study may be used to support an implementation and dissemination trial of Chinese EA within real-world behavioral health and social service settings.

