### Questionnaires/Instruments

#### MoCA Self-Reported Questionnaire

The MoCA self-reported questionnaire is the main method used for assessing cognitive function. To objectively measure the cognitive impairment patterns of the participants, MoCA, a sensitive, time-sparing tool with high diagnostic validity, will be used to measure the degree of chemobrain. We evaluate the utility of MoCA as a chemobrain screening test for older patients with cancer who are undergoing or about to receive chemotherapy. Participants will be instructed to self-report their cognitive functions through MoCA for 5 consecutive timepoints from baseline to the end of the 8-week treatment. Statistical software will be used to analyze participants’ cognitive function information recorded in case report forms.

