#### Sample Size Estimation

A total of 168 older patients with cancer will be recruited, of which 84 will be in the experimental group (EA) and 84 will be in the control group. Sample size calculation:

n = [p1 (1 – p1) + p2 (1 – p2)]/(p1 – p2)] × Cp.power

Cp refers to the process capability index. In the 2-sided test, Cp.power = 10.5 when *P*<.05 is met. n is the number of patients to be recruited in each group, p1 and p2 represent the incidence in each group, and a mean difference with 95% level of significance (α) and 80% power (1 – β) is set. In older patients with cancer, the incidence of chemobrain after chemotherapy is 30%, and the reduction of chemobrain could be 10%-20% with acupuncture intervention. The sample size for each group is 84 participants, considering a 20% dropout. Therefore, the overall target sample size of 168 will be included.

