### Statistical Analyses

Cognitive impairment is defined as those with SD>1.5 in the mean scores of MoCA and the QLQ-C30 at baseline for all participants at different timepoints. A time-series test in the Kaplan-Meier survival analysis will be used to compare the incidence of cognitive deficits accumulated after 8 weeks of acupuncture intervention between the 2 groups. Linear mixed-effects modeling will be used to compare participants’ cognitive impairment, fatigue, and depression at baseline, during, and after acupuncture intervention, where only those who have completed at least one assessment at baseline and during treatment will be compared. This model will use time and group as categorical fixed factors and random intercepts and use random intercepts in conjunction with a measurement covariance matrix. Participants’ age, chemotherapeutic drug dosage, fatigue at baseline, depression, and additional treatments will be considered as covariates in the statistical analyses. A 2-sided *t* test will be used to compare the covariates at each timepoint between the 2 groups. The chi-square test will be used for qualitative information and the *t* test will be used for continuous information at baseline. Statistical significance will be considered at *P*<.05. The study data used will be statistically analyzed using SPSS software (IBM Corp) under the supervision of a statistician. To ensure the privacy of the patients, all relevant study data and personal data will be kept in a locked file cabinet. Electronic data will be stored on an encrypted computer and will not be stored on any external storage device. Each participant will be assigned his or her own ID in the study record, which will be used in lieu of his or her name and personal identifying information. Clinical data from the study will be kept in a separate file from the participant’s personal data. The principal investigator will be responsible for all the clinical trial data. During and after the clinical trial, the principal investigator, researchers, and the ethical review committee have the right to view the study data. Participants will have the right to access their personal data and the results of the study. All study data will be stored for a minimum of 3 years after the completion of the trial, after which they will be destroyed in accordance with the rules of the ethics review committee.

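### The article does not name one primary outcome consistently, and the sample size and first-listed analysis rest on a further quantity, the incidence of impairment

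*Protocol article*

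**What the plan says.** The protocol article describes the primary outcome in three places.

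- **Abstract, Results:** "The primary outcome of this intervention will be the scores of the Montreal Cognitive Assessment".
- **Introduction:** "Changes in the scores on MoCA [17] and the incidence of adverse events serve as the primary outcome".
- **Methods, Assessments:** "The primary outcome of this study is to verify whether EA is therapeutically useful for preventing chemobrain and alleviating the related symptoms"; the sentence goes on to add the safety of the intervention. The next sentence reads "Cognitive performance will be assessed using MoCA + FACT-Cog". The list of secondary outcomes follows and does not include FACT-Cog.

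Under the MoCA instrument heading, the article also says "The MoCA self-reported questionnaire is the main method used for assessing cognitive function".

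Two further sections use a different quantity. Sample Size Estimation works from event proportions: "the incidence of chemobrain after chemotherapy is 30%, and the reduction of chemobrain could be 10%-20% with acupuncture intervention". Statistical Analyses opens its between-arm comparisons with "A time-series test in the Kaplan-Meier survival analysis will be used to compare the incidence of cognitive deficits", and defines impairment by a 1.5 SD criterion applied to MoCA and the QLQ-C30. Linear mixed models come next. One general threshold is given: "Statistical significance will be considered at *P*<.05".

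**The concern.** A confirmatory trial needs one result that decides it, or a stated rule for combining several. Here the Abstract gives one scale, the Introduction gives that scale plus a safety event rate, and Assessments gives an aim with two cognitive scales next to it. The calculation that justifies 168 patients concerns an incidence, which none of the three statements defines as the primary variable.

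A reader of the final report could not tell from this article whether a difference in MoCA, in FACT-Cog or in the incidence of impairment was the planned test. If these disagree, the article would support presenting more than one of them as primary, and the nominal 5% error rate would no longer describe the primary claim.

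**Working it through.** **Step 1. Set the statements side by side.**

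| Section | Quantity | Type |
|---|---|---|
| Abstract, Results | MoCA scores | Continuous scale |
| Introduction | MoCA change and adverse-event incidence | Scale plus safety event rate |
| Assessments | Prevention, symptom relief, safety; cognition by MoCA + FACT-Cog | Aim, with two scales |
| Sample Size Estimation | Incidence of chemobrain, 30% before reduction | Binary |
| Statistical Analyses, first comparison | Cumulative incidence of cognitive deficits over 8 weeks, impairment defined from MoCA and QLQ-C30 | Time to event |

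MoCA appears in each of the first three rows. FACT-Cog appears in one of them, by position. QLQ-C30 enters the event definition, although Assessments lists it as a secondary QoL measure. Assessments are planned at weeks 2, 4, 6 and 8, and none of the three statements says which one decides.

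**Step 2. Check what the planned size belongs to.** The plan's figure is 84 per group, with inputs p1 = 30%, a reduction of 10%-20%, the constant 10.5, 80% power and 20% dropout. Reading the reduction as 20 percentage points (p2 = 10%), the sum of variances is 0.3 × 0.7 + 0.1 × 0.9 = 0.30.

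- Formula as printed, difference not squared: 0.30 / 0.20 × 10.5 = 15.75.
- Usual form, difference squared: 0.30 / 0.04 × 10.5 = 78.75, so 79 per group; 78.75 / 0.8 = 98.4, so 99 with dropout.

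Neither form gives 84. That is a separate matter, and this point does not depend on it. What matters here is that every input is a proportion. No SD or target difference for MoCA is stated, so the 80% power is not a statement about MoCA.

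**Step 3. Illustrate the error rate.** Assume that two outcomes are each tested at two-sided 5% and that success on either suffices. Under independence:

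1 − (1 − 0.05)² = 1 − 0.9025 = 0.0975, or 9.8%.

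With correlated test statistics Z1 and Z2, the rate is 1 − P(|Z1| < 1.96 and |Z2| < 1.96) under a bivariate normal distribution:

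| Assumed correlation | Chance of at least one false positive |
|---|---|
| 0 | 9.8% |
| 0.5 | 9.1% |
| 0.7 | 8.3% |
| One outcome only | 5.0% |

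The article gives no correlation, so 0.5 and 0.7 are assumptions chosen to show the range.

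**The case against.** The best defence is that the three statements overlap more than they conflict. MoCA is in all of them, the Abstract names it alone, and the article calls it the main method for cognitive function. The Assessments sentence is an objective worded as an outcome. On this reading the trial has MoCA for efficacy, plus safety, loosely described. Much of this stands, and it makes MoCA the natural choice if one variable is to be kept. It does not remove the conflict: the Introduction adds a second primary item, Assessments puts a second scale beside MoCA, and the sizing and first comparison use incidence.

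FACT-Cog's place in the primary tier is an inference. No sentence calls it primary. The secondary list in Assessments also omits the Digit Span Test, which the Abstract and Introduction call secondary, so omission from that list is weak evidence. This stands, and FACT-Cog's status is best described as unclear.

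A reader might go further and infer that the article sets up rival primary outcomes, any of which would win the trial at an unadjusted 5%. The document does not support that:

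- Statistical Analyses gives one general threshold and names no test of FACT-Cog. A success or multiplicity rule may sit in an analysis plan that is not shown, so its absence is not the finding.
- Adverse events are treated as safety monitoring, and no reduction in them is claimed as proof of efficacy, so an error rate that counts them as a third route to success is not warranted.
- A calculation of the power to succeed on both scales would need a power for each. The stated 80% is for a binary incidence.
- A clean contrast between an objective MoCA and a subjective FACT-Cog is also unsafe, because the article describes MoCA as self-reported.

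**Conclusion.** The point holds as an internal contradiction in the current text: the primary outcome is not named consistently, and the sample size and first-listed comparison rest on a quantity that none of the three statements defines. It is a conflict between passages, so condensation for a journal does not explain it.

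The size can only be illustrated. If either of two outcomes sufficed, the false-positive rate would lie between 8.3% and 9.8% instead of 5%, assuming two-sided 5% tests and a correlation between 0 and 0.7. The article does not state an either-or rule; it leaves room for one.

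**What to change.** Before unblinding, name one primary variable, one between-arm measure and one timepoint; for example, the between-arm difference in MoCA total score at week 8 (T4). Use it in the Abstract, the Introduction and Assessments. List FACT-Cog as secondary and adverse events as a safety objective.

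Then align Sample Size Estimation and Statistical Analyses with the choice, in one of two ways:

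1. Make the incidence of impairment the primary outcome, and change the three outcome statements to match.
2. Keep MoCA as primary, label incidence secondary, and restate what the planned 168 can detect on MoCA, using an assumed SD and the 20% dropout.

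Naming MoCA in the three statements alone would not be enough, because it would leave the timepoint open and the sizing on a different outcome.

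The change is to wording and needs no new measurements. The article reports 11 participants recruited by 21 October 2023, so at that time it could be made early in the trial. The downside is that FACT-Cog can no longer carry a primary claim, and the stated 80% power may have to be restated. Whether 168 is enough for a MoCA mean difference cannot be judged from the article.

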#### FAACT Self-Administered Questionnaire

The FAACT is a self-administered questionnaire developed to assess symptoms in patients with cancer with limited food intake and decreased QoL. For FAACT, a cutoff value of ≤24 has been advised to assess anorexia based on the fact that it is the half of the maximum score than can be obtained [31].

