#### FACT-BRM Screening Tool

The FACT-BRM is a brief screening tool designed to assess the QoL in patients treated with BRMs. The FACT-BRM scale will be useful for measuring QoL in older patients with cancer who are receiving treatment with BRMs.

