At present, there is no responsive therapy for chemobrain. The current clinical medications are not effective for chemobrain prevention and therapy. Study and research literatures [14,15] suggest that Chinese acupuncture might be effective for relieving various discomforts caused by anticancer drugs, such as pain, vomiting, fever, fatigue, dry mouth, anxiety, depression, and sleep disorders. Several studies [11,13-16,30] have shown the efficacy of EA intervention in various neurological diseases. Compared with acupuncture, EA has reported to produce a higher intensity of stimulation on acupoints and is progressively being widely used for its adjustable strength, frequency, and easy quantification in clinical practice [14]. In addition, EA can promote the rehabilitation of pathological microstructures in the brain and improve the cognitive function of patients with cognitive impairment [16].

Our study aims to explore the feasibility, efficacy, and safety of using EA by involving multiple disciplines (oncology and Chinese Medicine) to treat chemobrain in older patients with cancer. Acupuncture itself has been demonstrated as a safe and effective treatment, and EA is a widely accepted and cost-effective alternative therapy option with low adverse effects for older patients with cancer. The findings of this study will provide useful information on determining a suitable therapy for chemobrain in older patients with cancer. EA may be ready for implementation and dissemination in real-world cognitive function settings consistent with the objectives outlined in this clinical trial’s strategic plan. Overall, this proposal has the potential to decrease neurocognitive symptoms among older patients with cancer—populations determined to be most at risk of exacerbated, long-lasting negative health sequelae. EA, if proven to be effective, can be implemented into routine settings to benefit older patients with cancer experiencing chemobrain. We believe that data from this efficacy trial will determine whether Chinese EA successfully alleviates the symptoms of chemobrain and whether these improvements could markedly reduce the various side effects due to cytotoxic chemical drugs.

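### By the protocol's own descriptions, FAACT and FACT-BRM do not support a broad statement about the side effects of cytotoxic drugs

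*Protocol article*

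**What the plan says.** Assessments (Methods) lists chemotherapy-induced side effects as one of four aspects of efficacy and as a secondary outcome: "the manifestation of chemotherapy-induced side effects will be assessed using the Chemotherapy Symptom Rating Scale FAACT + FACT-BRM". Study Procedures makes the same assignment, naming FAACT and "FACT-BRM) [28] for chemotherapy-related side effects".

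The instrument sections then describe the two scales:

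- **FACT-BRM Screening Tool:** "The FACT-BRM is a brief screening tool designed to assess the QoL in patients treated with BRMs". The next sentence calls it "useful for measuring QoL in older patients with cancer who are receiving treatment with BRMs".
- **FAACT Self-Administered Questionnaire:** "developed to assess symptoms in patients with cancer with limited food intake and decreased QoL", followed by a cutoff of 24 or less for judging anorexia.

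On treatment, Study Procedures says both groups receive "routine chemotherapy provided by their oncologists, which will include the use of cytotoxic drugs". The eligibility criteria require chemotherapy that is under way or about to start. They do not mention biologic response modifiers.

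On the intended conclusion, the Discussion says the data will determine "whether these improvements could markedly reduce the various side effects due to cytotoxic chemical drugs". The Introduction says nearly the same.

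**The concern.** The protocol labels the pair a chemotherapy symptom rating scale in one section, then describes neither member that way in the sections devoted to them. One is described as measuring a different construct (quality of life) in a differently treated population. The other is described as covering one symptom area.

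What is at stake is what may be concluded from this secondary outcome. As written, a between-arm difference in FACT-BRM, which the protocol itself describes as a quality-of-life score, would be reported as a difference in chemotherapy side effects. Quality of life is already a separate secondary outcome, measured by the EORTC QLQ-C30. The same kind of score would then feed two differently labelled claims.

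**Working it through.** No arithmetic applies. The point depends on no rate, effect size, power or sample size, and the plan gives no figure to reproduce. The check is to set the statements side by side.

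| Question | FACT-BRM | FAACT |
|---|---|---|
| Outcome assigned (Study Procedures, Assessments) | Chemotherapy side effects | Chemotherapy side effects |
| Construct in its own section | Quality of life | Symptoms linked to limited food intake; anorexia cutoff |
| Population in its own section | Patients on biologic response modifiers | Patients with cancer who have limited food intake and reduced quality of life |
| Population enrolled | Aged 60 or older, on or about to start chemotherapy | Same |

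**Step 1, construct.** For FACT-BRM, the assigned outcome (side effects) and the described construct (quality of life) differ. For FAACT they overlap in part, since appetite and food intake can be affected by chemotherapy, but the described scope is narrower than side effects in general.

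**Step 2, population.** The only treatment that eligibility and Study Procedures specify is chemotherapy including cytotoxic drugs. No section says that participants receive a biologic response modifier. The described population for FACT-BRM is therefore not the one the trial selects.

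**Step 3, claim against measure.** The Introduction and Discussion speak of side effects of cytotoxic drugs in the plural and without limit. The second aim also posits mediation through how often certain digestive, neurological and distress-related symptoms occur. FAACT plausibly bears on the digestive part. Neither instrument section describes its scale as giving the frequency of neurological or distress symptoms.

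**Step 4, other data in the plan.** Fatigue has its own scale (FACIT-Fatigue), and the QLQ-C30 measures quality of life. The Safety Assessment section has adverse events reported at each visit and graded by CTCAE v5.0. That collection is framed around the safety of the acupuncture, and neither Assessments nor Study Procedures links it to the side-effect outcome.

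**The case against.** The strongest reply is that the instrument sections are two-sentence summaries in a condensed article. They give no items, and a scale may cover symptoms its summary does not name. This stands. A reader might infer that the side-effect question cannot be answered from these scores at all, or that a change in FACT-BRM would be nothing more than a general quality-of-life change. The document does not support either inference, because without item content it cannot show that the scores carry no side-effect information.

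A second reply concerns the yardstick. It is tempting to count the eight symptoms in the Introduction and Discussion, from pain and vomiting to insomnia, and note that neither instrument section names any of them. That list reports what cited literature says about acupuncture. It is not this trial's outcome list, so the count proves little.

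Third, other data also bear on side effects (FACIT-Fatigue, QLQ-C30, the planned models of fatigue and depression, graded adverse events), and the broad claim is not said to rest on the two scales alone. This stands in part. Those data exist, but the plan assigns the side-effect outcome to FAACT and FACT-BRM only.

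Fourth, no rule excludes a biologic, and the Statistical Analyses section foresees additional treatments as covariates. Some participants may therefore receive one. Their share is unknown, so this does not establish that the scale fits the population as a whole.

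What survives all four replies is the mismatch between the outcome label and the protocol's own descriptions.

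**Conclusion.** The concern holds in a limited form. As the protocol describes them, FAACT and FACT-BRM do not support a broad statement about the side effects of cytotoxic drugs. FACT-BRM would enter the results under a label that its own section does not give it.

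The size is modest. One secondary outcome and the claims drawn from it are affected. The primary cognitive comparison, the target of 168 participants and every stated figure are untouched. How far any score would shift because of the mismatch cannot be computed from the document.

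The conclusion rests on two assumptions: that the instrument sections describe the scales fairly, and that participants are not generally treated with biologic response modifiers, which the document neither states nor rules out. It does not extend to saying that the scales are uninformative about side effects.

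**What to change.** In Study Procedures and Assessments:

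1. Report FACT-BRM as a supportive quality-of-life score beside the QLQ-C30, in all participants. Do not restrict it to those receiving a biologic. That subgroup is of unknown size and could be defined by treatment started after randomization.
2. Report FAACT as an appetite and food-intake outcome.
3. Base any side-effect statement on a between-arm summary of the CTCAE v5.0 graded events recorded at each visit: per-patient incidence and worst grade over the 8 weeks, whatever the attributed cause. Add this alongside the questionnaires; it does not replace them.
4. If item 3 is not adopted, narrow the statements in the Introduction and Discussion to what the scales measure.

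Items 1, 2 and 4 cost only wording. Item 3 may need more. The Safety Assessment section speaks of events during acupuncture treatment, which can be read as the needling sessions alone, so recording would have to be stated to cover the whole 8 weeks. The earliest participants may then have less complete event data: 11 had been recruited by October 21, 2023, which is 11/168 = 6.5% of the target. The change should be dated, and the summary should note from which participant the wider recording applies.
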